#### Intervention group

Early enhanced occupation-based therapy is limited in the ICU. Identification of appropriate occupation-based therapy is dependent on cognitive (arousal, attention, executive functioning), physical (strength, co-ordination) and physiological restrictions (ventilator, cardiovascular status, medications). Co-morbidities, such as delirium, are assessed daily prior to the session and may result in session adaptation to maximise participation. Prior to engaging in early enhanced occupation-based therapy with the therapists, all patients will have received daily medical clearance by the treating physician. Clear physiological norms are established prior to participation to ensure that the occupation-based therapy is within the physiological capabilities of the participant [42]. A precautions checklist will be completed prior to each therapy session to ensure medical stability and clearance for activity participation. The checklist was created based on expert consensus guidelines for mobilisation in the intensive care unit and adapted to functional and cognitive participation requirements [42]. See Table 2 for contraindications to treatment. Monitoring of cardiovascular and respiratory status during early enhanced occupation-based therapy is completed by the bedside ICU nurse. Session termination will be under the guidance of the bedside nurse in collaboration with the occupational therapist and will be based on changes in cardiac and respiratory function as well as patient request to stop. Any immediate change that results in a contraindication being identified will lead to session termination. Further guidance on therapy discontinuation will be in line with published guidelines for exercise termination [43, 44] and includes a drop in systolic blood pressure, signs of myocardial infarction, unusual shortness of breath, arrhythmias, angina or signs of poor perfusion.

**Table 2 Tab2:** Checklist for contraindications to intervention

- O_2_ Saturation < 90% - Respiratory Rate > 30 bpm - Fi O_2_ > 0.6 - PEEP > 10 cm H_2_O/ventilator dysynchrony - Any rescue therapies (NO, Prostatcyclin, prone) - Significant antihypertensive medications - MAP (below target, various support measures) - Bradycardia on significant pharmacological support - Tachycardia > 150 bpm - RASS > 2+ - Large open wound/uncontrolled active bleeding	

Patients will undergo sedation breaks during which targeted early enhanced occupation-based therapy will be delivered. The therapist will carry out the intervention to a maximum of 60 min per day, based on graded performance and localised adaptation from response level, such that sessions may be carried out twice a day (30 min each) to 3 times a day (20 min each) or a single session with a higher level patient (60 min). The measure of 60 min has been chosen to comply with perceived expectations of rehabilitation unit therapy intensity and duration per profession [45]. Where the full quota of therapy is unable to be provided, clear reasons for therapy termination will be gathered on the data form and analysed.

Prior to engaging the patient in early enhanced occupation-based therapy, participants will undergo simple cognitive and physical assessments to enable the therapist to adapt the chosen task to optimise performance and ensure that cognitive stimulation is appropriate. Pre-intervention measures include the following:

Richmond Agitation and Sedation Scale (RASS) [46] measures level of sedation and agitation. Patients will receive treatment if they fall within − 2 to + 2 scales. Patients falling on either extremes are deemed unsuitable for engagement at the current time point, although will be assessed regularly throughout the day prior to therapy, to ensure all opportunities for engagement are taken.

Glasgow Coma Scale (GCS) [47] measures arousal and response level in patients with severe injuries and is used to identify initial emergence of recovery post-sedation withdrawal. The highest score is 15 (fully oriented and alert) and the lowest score is 3 whereby a patient is considered unresponsive. The GCS will be completed prior to the treatment intervention as this will guide the therapist in providing either sensory stimulation [48, 49] or early enhanced occupation-based therapy.

The Confusion Assessment Measure ICU (CAM-ICU) [50] is an assessment of confusion in the early identification of delirium of patients within the intensive care unit. The presence of delirium will not limit participation within an early enhanced occupation-based therapy session. Strategies will be used to increase attention and encourage sequencing of short subtasks in order to complete a full grooming or self-care task.

The Short Portable Mental Status Questionnaire (MSQ) is a brief orientation checklist used to demonstrate current and previous memory linked to orientation. It is a 10-statement questionnaire that is easily administered at the bedside [51] and gives a therapeutic indication of ability to follow questions and commands and engage in therapy. A lack of orientation as evidenced through poor scoring on the MSQ will lead to the therapists including orientation cognitive tasks to facilitate cognitive recovery within the early enhanced occupation-based therapy. Strategies such as auditory retrieval priming (for example if yesterday was Tuesday then today is…) and errorless learning will be used to facilitate cognitive orientation recovery [52].

Early enhanced occupation-based therapy covers a range of activities of daily living including, but not limited to, grooming activities carried out in bed, grooming activities at the beside, grooming in the ICU bathroom, strip washing and self-care in the bed or bedside and showering in the ICU bathroom. Additional activities include leisure tasks related to board games, creative artworks, computer or iPad usage, adult mindfulness colouring in and functional grooming (manicure/makeup) and are identified based on completion of a leisure interest checklist as documented by the relevant next-of-kin or close family member (under consent guidelines). Activities are adapted through use of equipment, set-up, positioning and number of subtasks planned, to enhance participation outcomes and rehabilitation goals.

Cognitive stimulation tasks are often incorporated within the early enhanced occupation-based therapy through active engagement such as reality orientation, choice making and decision making, task sequencing directions, use of familiar objects, faces or smells, use of familiar music, participation in appropriately cognitively challenging games such as Sudoku and mindfulness colouring in, and reminiscence and recall challenges. The development of rapport supports engagement and enables the therapist to set appropriately challenging activities thereby enhancing participation and achievement of goals. Family engagement is another source of cognitive and functional activity and patients may ‘make something’ or video record a message for their family member where possible. Cognitive retraining involves the careful selection of appropriate strategies including but not limited to errorless learning, backward and forward chaining, vanishing cues and auditory priming [52].

Sensory stimulation tasks may be carried out in patients with a lower arousal level [48, 49, 53, 54]. Environmental adaptations (temperature of water, roughness of flannel) will be used to participate and adapt the tasks for heightened controlled sensory stimulation. Patients with lower levels of arousal will predominantly participate in regular shorter sessions with a focus on a tactile, auditory and visual stimulation within an occupation-based (hand-over-hand) task.

A manualised intervention strategy will be followed to ensure consistency of approaches; however, interventions will be personalised to facilitate increased participation and enhanced triggering of memories. A non-standardised leisure checklist or interview will be used to identify pre-morbid interests and lifestyle choices that can be incorporated within the session to enable appropriate choice of activity and topic discussion where relevant to stimulate cognitive recovery. The lifestyle/leisure checklist is based on the Person-Environment-Occupational Performance Model (PEOP) which serves as a framework for occupational therapy practice [55]. The checklist will also incorporate other regularly used client-centred checklists and models such as the Sunflower Chart developed by the Dementia Management and Advisory Service (DBMAS) for patients with a cognitive impairment, Model of Human Occupation (MOHO) [56] Interest Checklist and the culturally relevant Kawa Model [57]. This combination of approaches enables the therapist to develop a comprehensive list of activities and interests that could be used to facilitate participation and patient engagement. Table 3 lists the early enhanced occupation-based therapy and cognitive stimulation tasks carried out as part of the intervention.

**Table 3 Tab3:** List of intervention therapy provision

Outcome measure				Occupation-based task	Cognitive stimulation task
GCS	RASS	MSQ	CAM	Function	Cognition
**3–8**	**− 2 to 0**	**0**	**+ve or −ve**	• Hand over hand facilitation of o Wiping face o Brushing teeth o Skincare o Oral care o Brushing hair o Washing upper body o Moisturising upper body	• Orientation prompts • Sensory stimulation—visual and auditory search and locate games • Communication/yes /no to simple biographical/physiological details—use adapted communication methods (visual, gestural based on ventilation status)
**8–12**	**− 1 to +2**	**0**	**+ve or −ve**	• Hand over hand facilitation of o Wiping face o Brushing teeth o Skincare o Oral care o Brushing hair o Washing upper body o Moisturising upper body • iPad activities including facetime relatives • Active assisted facilitation of o Wiping face o Brushing teeth o Skincare o Oral care o Brushing hair o Washing upper body o Moisturising upper body o Dressing while seated o Table top activities including games, creative work, cognitive stimulation, iPad challenge games o Upper limb activity programmes (e.g. theraputty, colouring in, creative work)	• Orientation • Sensory stimulation—visual and auditory search and locate games • Communication/yes/no • Reminiscence/recall therapy • Goal planning/structured day planning (participation and idea generation)
**13–14**	**0 to +2**	**1–10**	**+ve or −ve**	• Hoist transfer to commode for assisted showering or grooming at basin in ICU bathroom • Standing transfer to commode for assisted showering or grooming at basin in ICU bathroom • Stand transfer onto shower bench for assisted or supervised showering with task set-up depending on physical and cognitive abilities	• Orientation • Sensory stimulation—visual and auditory search and locate games • Communication/yes/no • Reminiscence/recall therapy • Goal planning/structured day planning (participation and idea generation)
**15**	**0 to +2**	**1–10**	**+ve or −ve**	As above but increasing choice making, initiation and independence required through task set-up, environmental challenges and attention / cognition challenges (rate of task performance, number of distractors, error recognition)	• Reminiscence/recall therapy • Goal planning/structured day planning (participation and idea generation) • Problem solving challenges, e.g. games, iPad use including facetime

### Adaptation of the MSQ and cognitive response tasks

Based on the frequency and nature of intensive care where patients may be ventilated or have poor attention span, adaptive strategies will be required to facilitate choice and communication in completing the MSQ and participating in cognitive tasks. This is managed via multiple methods:
Multiple choice written answers on laminated card: options vary between 3 and 10 per page pending arousal level. It is recommended that 3 options be used for ease with visual clues. Therapist can read out answers and request a yes/no pending communication, or if motor activity available, patient can select option.Multiple choice verbal answers: maximum of 3 options read to patient with use of head nod or agreed communication method for yes/no (thumbs up/down, blink pattern).White board or written answers to questions—provide adapted writing equipment (for poor grip strength) and whiteboard/paper positioned to allow maximum participation.Mouthing or vebalisation in tracheostomy patients as able.Alphabet board with large font for patient who can spell but not write—use technique as per communication method for eye scanning methods.

The intervention will be provided face-to face by the trained therapists and may occur in bed, at the beside or within the intensive care unit bathroom.

All occupational therapists expected to work within the intensive care unit will be trained and become familiar with the intervention manual prior to the study. All interventions will be delivered by the two trained specialist critical care occupational therapists based on the intervention manual. Training will be provided by the principal investigator ([name]) over a 3-month period incorporating observation and clinical reflection examples. Two reserve therapists whose primary caseload is not in the intensive care unit will be trained by [name] to ensure all functional sessions can be completed even in absence of usual critical care staff (for example due to annual leave or unexpected absence). Treatment fidelity will be monitored through case notes and discussion of therapy goals prior to session delivery. Any significant modifications (which exclude personalisation of therapy content delivery) will be discussed with the chief investigator prior to delivery.

#### Qualitative follow-up

Part 2 of this study includes a qualitative component and will be guided by interpretive description [58] to explore the lived experience of participants receiving the intervention and the perception of family members or the most involved significant other. At 90 days post-randomisation, all patients from the early enhanced occupation-based therapy group will be invited to participate in in-depth semi-structured interviews targeted towards exploring their experience of engaging within the early enhanced occupation-based therapy. In the event that the participant is too unwell to physically attend an interview, alternative arrangements, such as telephonic interview, will be offered.

The person responsible will be provided with a separate information and consent form to participate in the interview.

Interviews will be conducted by the principal researcher in a private, wheelchair accessible room at Logan Hospital. Funding for transport will be provided to facilitate attendance at interviews. Wheelchair accessible transport will be organised for participants who require specialist accessibility options. Interviews will be audiotaped and transcribed verbatim by a transcription service.

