### Participants

The study will be conducted in a Queensland level two adult eight-bed intensive care unit at Logan Hospital, Brisbane, Australia. All patients admitted to the intensive care unit will be included if they are aged over 18 years and are expected to require invasive mechanical ventilation for greater than 48 h.

Patients will be excluded from the trial if:
They are admitted to the intensive care unit but do not require mechanical ventilation.They have been readmitted to the intensive care unit from the current hospitalisation.A withdrawal of treatment is expected to occur within the next 24 h or they are not expected to survive the current intensive care unit admission.They have a poor level of functional ability prior to admission (requiring carer assistance/high dependency level in activities of daily living as measured by a Modified Barthel Index score < 40).They have a pre-existing severe cognitive deficit (as identified by completion of the short form IQCODE with an average score above 3.31–3.38).They have a pre-existing significant mental health disorder impacting on participation.They live interstate and would be unable to attend the 90 days post-randomisation follow-up in person.They are unable to communicate in English.

Patients admitted over the weekend where occupational therapy intervention cannot be immediately initiated will be eligible to participate in the trial, and therapy will begin on the first working day.

The 90-day post-randomisation evaluations’ timepoint for the follow-up review date has been chosen based on the funding cycle. As this is a pilot feasibility study and the study is limited in duration, this time point was chosen to be sufficiently representative to identify if patients had ongoing concerns, and to ensure their memory of the therapy provision was current for the semi-structured interviews.

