### Outcome measures

#### Primary outcome measure

Independence within activities of daily living will be measured using the Functional Independence Measure (FIM™). The FIM will quantify the participant’s functional and cognitive status at intensive care unit and hospital discharge, as well as at 90 days post-randomisation. This tool is validated for use in the critically ill population [60, 61] and provides reliable information regarding patient functional change during rehabilitation across various hospital and community settings [62]. The FIM will be conducted within 24 h of the expected discharge from the intensive care unit and hospital or on the Friday before the expected discharge, if likely to occur over the weekend. It will also be administered during the 90-day follow-up session. The FIM will be performed by an occupational therapist blinded to participant assignment groups and who does not actively work on the intensive care unit.

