### Data analysis

All data from the case report forms (CRF) will be entered into a purposefully designed Excel database and exported into SPSS version 22.0 for analyses. Descriptive statistics will be used to determine the distributions of the data for the intervention and control groups and to test whether statistical assumptions for parametric tests are achieved. Imputation will be used to correct for missing data. Continuous variables that are normally distributed will be compared between the groups at each follow-up using an independent groups *t* test. Effect sizes will be calculated using Cohen’s *d*. Non-parametric analysis will be conducted for continuous variables that are not normally distributed. Categorical variables will be compared with the chi-square statistic. A *p* value of 0.05 will be considered statistically significant. Where appropriate, analyses will be reported with mean differences and 95% CI. Previous values from the same patient will be used for missing data.

In particular, objectives will be analysed as follows:
The utility of the selection of outcome measures will undergo sensitivity analyses in relation to the ease with which they can be administered and will relate to missing data and the identification of both univariate and multivariate outliers. The effect size for the primary outcome variable will be used to determine the required sample size for a fully powered trial.Recruitment and consent rates will be collected and analysed to determine the feasibility of recruiting form the chosen population. The inclusion and exclusion data (screening log) will be summarised and will influence further protocol changes when considering progression to a full scale randomised controlled trial.Retention rates in response to follow-up procedures (attendance at interviews) will be analysed to identify any trends that may influence further trial progression.The intervention data will undergo sensitivity analyses in relation to non-compliance, the intention to treat per protocol in addition to as treated. Protocol violations regarding the intervention manual strategies will be noted.The intervention effect will be analysed through the use of the above outcome measures, and further analysis of case notes will reveal common trends in treatment adaptation or selection, based on the structure of the intervention manual.

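### As worded, transport at 90 days is funded only for interviews offered to the intervention arm, while both arms must attend in person for the outcome assessment, so attendance can differ by arm for a reason the trial creates

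*Protocol article*

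**What the plan says.** All references are to the protocol article.

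- **Travel support.** Under Qualitative follow-up: "Funding for transport will be provided to facilitate attendance at interviews", followed by "Wheelchair accessible transport will be organised for participants who require specialist accessibility options". Patients too unwell to come are covered by "alternative arrangements, such as telephonic interview, will be offered". The article mentions transport nowhere else.
- **Who is interviewed.** The same section says "all patients from the early enhanced occupation-based therapy group will be invited to participate in in-depth semi-structured interviews". Significant others are also interviewed. Controls are not.
- **Who is assessed at 90 days.** Table 4 (Data collection) schedules FIM, MBI, grip strength, MoCA, SF-36 and HADS at 90 days, with no distinction by arm. On the FIM, the Primary outcome measure section says "It will also be administered during the 90-day follow-up session".
- **In person.** One exclusion criterion under Participants reads "They live interstate and would be unable to attend the 90 days post-randomisation follow-up in person". Grip strength is taken with a dynamometer, which also needs the patient to be present.
- **Use of the data.** Under Data analysis: "Continuous variables that are normally distributed will be compared between the groups at each follow-up", and for gaps, "Previous values from the same patient will be used for missing data". The same section takes the next trial's sample size from the effect size on the primary outcome.
- **Retention.** Table 1 sets 75% retention to follow-up as the line for proceeding, with no reference to arm. Aims and objectives and Data analysis both explain retention, in brackets, as attendance at the interviews.

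**The concern.** Two survivors with the same disability, one in each arm, are due the same assessment at the same hospital. As the text stands, only the intervention patient is stated to receive funded or accessible transport. The help is attached to an activity that belongs to one arm, so allocation itself can change the chance of attending.

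The barrier that transport removes is poor mobility, and the primary outcome measures independence in daily activities. Missingness at 90 days could thus be related to both arm and outcome.

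Two products of this feasibility trial are exposed. The first is the retention rate, which decides progression and would partly measure the transport offer. The second is the 90-day FIM difference, at the only time point after hospital discharge. The article's Limitations section already names attrition at follow-up as a risk.

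**Working it through.** The sample size of 30 rests on pilot-trial recommendations, so there is no power calculation to reproduce. At 1:1 allocation, 30/2 = 15 per arm, which agrees with the 15 intervention patients planned for the interviews. The attendance rates, gains and selection strengths below are assumptions; the article gives none.

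**1. Is the support arm-specific as written?** Transport is tied to interviews, interviews to the intervention arm, and the in-person assessment to both arms. The article does not state that interview and assessment share one visit. However, the Abstract places the interview at the follow-up, and the Participants section chose the 90-day point partly so that patients would still remember the therapy when interviewed. It is a fair assumption that transport to one brings the patient to the other.

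**2. Retention criterion.** 0.75 × 30 = 22.5, so 23 patients are needed. If all 15 intervention patients attend, 23 − 15 = 8 controls are enough, and 8/15 = 53%. The pooled rule can therefore pass while barely half the control arm is retained.

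**3. Would the data reveal an imbalance?** Three assumed pairs of attendance rates, each averaging 75%, were tested with 15 per arm (two-sided 5%, normal approximation):

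| Intervention v control | Difference | Power to detect it |
|---|---|---|
| 80% v 70% | 10 points | 9% |
| 85% v 65% | 20 points | 24% |
| 90% v 60% | 30 points | 47% |

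Even a 30-point gap would be missed about half the time.

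**4. Bias if earlier values are carried forward.** Assume no treatment effect and the same mean gain, in SD units, between last value and day 90 in everyone. Each arm's mean is then too low by (1 − attendance) × gain, so

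bias (intervention − control) = (attendance in intervention − attendance in control) × gain.

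- Gain 0.5 SD: 0.10 × 0.5 = 0.05, 0.20 × 0.5 = 0.10, 0.30 × 0.5 = 0.15 SD.
- Gain 1 SD: 0.10, 0.20 and 0.30 SD.

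All of these favour the intervention.

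**5. Bias in a complete-case comparison.** Two calculations were made, again with no treatment effect.

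- *Selective attendance in controls only.* With 65% of controls attending, fitter patients more likely to come (logit slope 0.5, 1.0 or 1.5 per SD of function), and intervention attendance unrelated to function, simulation puts the attending controls' mean 0.17, 0.29 or 0.38 SD too high.
- *Worst case in both arms.* If the share p lost is exactly the lowest-scoring, the observed mean rises by φ(z_p)/(1 − p). With 5/15 controls and 2/15 intervention patients lost, the rises are about 0.55 and 0.25 SD, a net of 0.55 − 0.25 = 0.30 SD.

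Both work against the intervention, the opposite direction to step 4.

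**6. With equal support in both arms,** the attendance difference created by the transport offer is zero, and so are the bias terms that depend on it.

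**The case against.** **Silence is not refusal.** The article nowhere denies transport to controls, and it points to a full protocol held in the trial registry. Travel arrangements are the kind of detail a journal article condenses. This stands: a reader might infer that a disabled control has no funded way to reach the assessment, but the article shows only that no such support is stated.

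**The key word is loose.** The closing words of the funding sentence reappear in brackets in the retention objective, where they explain follow-up in general and are not limited to one arm. The wheelchair sentence speaks of participants without naming a group. The authors may have meant every 90-day visit. This also stands, and it is a reason to clarify the wording. It does not remove the point, because the sentence sits in a section about interviews that one arm alone is offered.

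**The telephone option narrows the gap.** The sickest intervention patients may be interviewed without travelling, so funded transport need not bring them in for the FIM. This is fair. It reduces any difference among the most unwell, but not among patients who could attend if transport were arranged.

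**A masked benefit is not established.** A reader might infer that losing disabled controls hides a benefit. That holds only for a complete-case analysis, and its size is exaggerated if losses in the intervention arm are ignored. The article's own rule of using previous values can push the result the other way.

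**The stakes are those of a pilot.** FIM is also measured at ICU and hospital discharge, and the Discussion concedes that the study is not powered for clinically significant change. This is true, but retention is a progression criterion and the FIM effect size feeds the next trial, so the pilot's outputs still matter.

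**Conclusion.** The point holds as a defect of wording with a real consequence if the text is followed. Travel support at 90 days is stated for one arm's interviews, while the in-person assessment applies to both arms. Attendance can differ by arm for a reason related to function. A pooled 75% retention rule could conceal this (15/15 with 8/15 passes), and 15 per arm would often fail to reveal it.

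The 90-day comparison can be biased in either direction. The illustrations run from 0.05 to 0.30 SD toward the intervention with values carried forward, and from 0.17 to 0.38 SD against it among attenders. They rest on assumed attendance, recovery and selection, so neither direction nor size can be determined from the article. They also assume that interview and assessment fall on one visit and that controls do not in practice receive the same help.

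The article does not support two further readings: that controls are refused transport, or that invitations and reminders differ by arm. This is a cheap improvement to make before more patients reach day 90, since values lost at that visit cannot be recovered afterwards.

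**What to change.** In the Qualitative follow-up section, or better where the 90-day assessment is described, state that the same transport funding and wheelchair-accessible transport are offered to all participants in both arms for the 90-day outcome assessment, whether or not they are interviewed. If this was always intended, or the full protocol already says so, one sentence settles it.

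In Aims and objectives, Table 1 and Data analysis, define retention as completion of the 90-day outcome assessment, and report it by arm as well as overall.

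The cost is return transport for up to 15 control patients and a few lines of text. No visits, staff or procedures are added, because controls are already due this review. The sample size does not change.
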